### Blinding

Patients are told to receive physiotherapy but are blinded to allocation of the two treatments; the content of the treatments is not described in the information leaflet. This enhances the quality of the study, because the patients themselves measure the effect of treatment. GPs are also blinded for allocation to prevent accidentally informing the patients of the allocated treatment. The physiotherapists are not blinded for allocation, but the physiotherapists from each treatment group are kept strictly separate and are not involved in the outcome measurement. Finally, the primary investigator is blinded for patients' allocation but the research assistant is not; neither is involved in the outcome measurement.

### Physiotherapists and Interventions

After receiving written information, 34 physiotherapists in region West Brabant will participate in either the physiotherapy treatment (PT) or the graded activity programme (GAP). To optimise the contrast between the two treatments, both groups are strictly separated throughout the study. The PT group consists of 16 physiotherapists and the GAP group of 18 physiotherapists. The PT physiotherapists participate in a meeting to standardize the physiotherapy treatment. The GAP physiotherapists are instructed on the behavioural graded activity approach during a two-day theoretical and practical training course.

Both interventions are performed in an outpatient setting. A maximum of 18 treatments per patient is set and each treatment takes about 30 minutes, which is in accordance with medical insurance policy in the Netherlands. Before treatment starts, physiotherapists receive a completed questionnaire about the patient's main complaints [29]; this questionnaire reveals the three daily activities which are considered the most important complaints to the patient. Physiotherapists can use these three activities in the process of formulating the patient's primary therapy aim. In both treatments, the physiotherapist starts with a physical examination of the patient and an anamnesis. Then an individually tailored program will be applied and the process recorded after each treatment session using a specially designed form.

#### The physiotherapy treatment

The content of the physiotherapy treatment is decided by consensus among the participating PT physiotherapists. Treatment is according to a biomedical model, which implies guidance based on the amount and severity of pain that the patient experiences.

By consensus, the physiotherapy treatment is divided into the patient's primary therapy aim, three general treatment goals, and several techniques to attain those goals. The primary therapy aim is defined as the result the patient wants to achieve by the end of therapy. A general treatment goal is a goal for each single treatment and could, therefore, differ per treatment session. Table 1 shows the three general treatment goals, together with the techniques physiotherapists can choose to attain them. In daily practice a broad spectrum of treatment techniques are available, but in this study the techniques to be used consist of physiotherapy techniques with a strong focus on exercises. Moreover, manipulative techniques, acupuncture and other (alternative) techniques are excluded, as are physiotherapeutic applications such as ultrasound or diathermy.

#### Behavioural graded activity

An operant approach was the basis of the behavioural graded activity programme as used in this study. The treatment is according to a biopsychosocial model, which implies that it is guided by the patients' functional abilities and that time-contingent methods are used to increase the activity level of the patient [11]. The behavioural graded activity programme has three phases; a baseline phase, a treatment phase, and a generalization phase. These phases are not bound to strict time limits but can gradually merge into each other.

Before starting the baseline phase, the treatment vision and the patient's ideas about pain and its causes are discussed. The development and maintenance of pain will be explained and patients are reassured that it is safe to move and to increase their level of activity [11,13,30]. Both are explained by means of a pain model, which has been derived from the fear-avoiding-model of Vlaeyen et al. [13]. Thereafter primary therapy aims are formulated based on the patient's main complaints, which are described as three daily activities and were revealed in the baseline questionnaire. For each of these activities, a baseline level of intensity is determined based on a pain-contingent measure. This means that patients perform each activity at least three times, each time until they have to stop because of their pain. Afterwards, patient and physiotherapist together set a start quota and time-contingent treatment quotas for each activity. The quotas will be based on the patient's mean baseline scores, primary therapy aims [17], and on the behaviour that can be derived from the baseline measure. If necessary, facilitating disorder-oriented exercises can be added to the treatment as preparation for the activities that were pointed out as main complaints. The same approach as used for the main complaint is used for these exercises.

During the treatment phase, patients systematically increase the time-contingent quotas to enable them to reach their personal aims within a pre-set therapy time period. To ensure a successful experience during the first exercise, the start quota is below the mean baseline score. The pre-set exercise quotas have to be strictly followed; neither over-performance nor under-performance is allowed. During this phase the patient has to practice at home and document every activity or exercise on a performance chart. These charts will be discussed in the following treatment session and achievements will be reinforced while disregarding pain behaviours. Positive reinforcements of healthy behaviour and the patient's experiences of success are considered to be important to enhance the patient's motivations.

The generalization phase takes place at the end of the treatment phase. In this phase generalization of learned behaviour and management of relapses will be discussed.

### Outcome measurement

Baseline questionnaires are sent after inclusion, which is as soon as possible after patients have consulted their GP. Outcome of intervention will be assessed at 4 and 9 weeks after randomisation; however, if the treatment is not finished at 9 weeks, the patients will receive an additional questionnaire (Ts) after finishing the treatment. Follow-up assessments are planned at 26 and 52 weeks after randomisation.

All outcome measures are reported by means of mailed questionnaires. Table 2 presents the outcome variables, the instruments used and the moments at which they are measured.

Primary treatment outcome of this study is the global perceived effect, which is used to assess recovery from the complaint [31]. In addition, the global perceived effect in daily functioning was explored in order to also establish impact of treatment on daily activity. Both treatment outcomes (recovery of complaint and functioning in daily activity), are assessed on a 7-point Likert-scale, ranging from completely recovered (1) to worse than ever (7).

Costs are measured using a combination of questionnaires to collect data on direct medical costs (e.g. the amount of received treatment and additional therapy received), and indirect costs due to sick leave and disability.

Secondary outcome measures include main complaints, pain intensity, medical consumption, coping, functional status, quality of life, and psychological variables. Prognostic factors are measured including demographic variables, the baseline variables and the psychological variables (table 2).

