## Background

### Prevalence and incidence

Neck pain is a common complaint that causes substantial morbidity in western countries with a reported prevalence ranging from 9.5 to 22% [1,2]. Of all musculoskeletal pains in the Netherlands, neck pain is one of the three most reported with a point prevalence of 21%; it is more often reported by women than men [3]. In 1996 total related costs were estimated to be US $686.2 million, which is about 1% of the total Dutch health care expenditures [4]. Most neck complaints are continuous or recurrent [3]. When the neck pain persists for more than 3 months it is defined as chronic, and the related prevalence is 14.3% [3,5]. Although the prevalence of neck pain is stable over different age groups, the incidence of chronic neck pain increases with age [3,6].

There are many potential causes of neck pain, but mostly no specific underlying pathology is found so that it is designated as non-specific [7]. Although not a life- threatening disease, neck pain can negatively affect patients' quality of life, cause pain and stiffness, and may result in substantial medical consumption, absenteeism and disability [4,8].

In the Netherlands, patients with neck pain are often referred for physiotherapy. Moreover, physiotherapy accounted for 84% of the total direct medical neck pain costs in 1996 [4]. Although physiotherapists can apply various treatments, no formal guidelines are yet available.

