### Analyses

Descriptive statistics will be used to examine comparability of baseline data between PT and GAP, and to check if randomisation was successful. Before this analysis, decisions about differences considered to be clinically relevant are made and, if necessary, adjustment will be made for these differences in multivariate analysis. Further, all outcome data will be screened for normality and, if necessary, logarithmic transformations or non-parametric methods of analysis will be applied.

The first aim is to evaluate the clinical and cost effectiveness of GAP compared to PT. Clinical effectiveness will be examined with a Student's t-test (continuous), a Chi-square test (dichotomised) or a Wilcoxon test (not normally distributed) according to the intention-to-treat principle. This means that patients will be analysed in the treatment group to which they are randomly allocated. For missing data, imputation techniques will be used. When the dropout rate is 10% or more, or loss to follow-up is 20% or more, per-protocol analysis will be performed. The results on primary outcome will be dichotomised into improved versus not improved. Improved implies completely recovered and much improved, whereas not recovered implies slightly improved, not changed, slightly worsened, much worsened, and worse than ever [31].

Cost effectiveness will be calculated from a societal perspective. Costs (direct as well as indirect) will be related to the treatment effects, based on the primary outcome measure, by calculating cost-effectiveness ratios.

The second aim is to identify subgroups of patients that benefit most from one of the two treatments. The following subgroups will be investigated: duration and severity of the complaint, depression, and fear of movement.

The third aim is to identify important variables for recovery. For this purpose multivariate analysis will be performed to investigate the influence of prognostic variables and patient characteristics on the outcome. Separate analyses will be conducted to investigate prognostic factors for short-term (3 months) and long-term (12 months) recovery.

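### Session counts for the cost analysis are taken from questionnaires, although a form is completed after every treatment session in both arms

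*Protocol article*

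**What the plan says.** Four sections of the protocol article bear on this point.

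- **Outcome measurement** gives the source of the cost data: "Costs are measured using a combination of questionnaires to collect data on direct medical costs (e.g. the amount of received treatment" is followed by additional therapy and by indirect costs from sick leave and disability. The sentence does not say who fills in the questionnaires. The same section states: "All outcome measures are reported by means of mailed questionnaires". Assessments fall at 4, 9, 26 and 52 weeks, with an extra questionnaire (Ts) after the end of treatment if it runs beyond 9 weeks.
- **Physiotherapists and Interventions** sets the limits of treatment: "A maximum of 18 treatments per patient is set and each treatment takes about 30 minutes". For both treatments it adds: "Then an individually tailored program will be applied and the process recorded after each treatment session using a specially designed form".
- **Blinding** treats effect measurement as the patient's task ("because the patients themselves measure the effect of treatment") and keeps the unblinded physiotherapists out of it.
- **Analyses** makes cost effectiveness part of the first aim, from a societal perspective.

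No section says that the session forms feed the cost analysis, and none says that they do not.

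**The concern.** The plan fixes only a maximum number of sessions, and the programme is tailored to the individual, so the number delivered will vary between patients. Each session enters the direct medical cost. The trial will hold two possible sources for that number: what is reported by questionnaire, and a form made at the time of each session. The article names the first.

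A remembered count can be wrong, and an unreturned questionnaire can leave no count at all. Patients who stop treatment early may also be the ones who stop replying, so the missing counts need not resemble the observed ones. The forms do not depend on memory or on the post, and they exist for the sessions that an early leaver did attend. At stake are the precision of the treatment-cost comparison between arms and, if missingness or misreporting differs by arm, its freedom from bias.

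**Working it through.** The article gives no figure for session counts that could be reproduced. Its only sample-size figure (160 patients, 80 per arm) concerns global perceived effect and has no bearing here. The check is mainly a reading of the sections together.

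**1. What is the named source?** Outcome measurement says questionnaires for costs and mailed questionnaires for all outcome measures. Blinding has patients as the reporters and excludes the physiotherapists. Together these point to a patient-reported count, although the cost sentence itself names no respondent.

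**2. Is there a better source in both arms?** Yes: "the process recorded after each treatment session using a specially designed form". The sentence follows from an opening that covers both treatments. One form per session means that counting forms gives the number of sessions, whatever else the form contains.

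**3. Are the two connected?** No section connects them.

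**4. How much can the count vary?** The stated limit is 18 sessions of about 30 minutes, which is 18 × 30 = 540 minutes, or about 9 hours of treatment per patient. An error of one session is 1/18 = 5.6% of that maximum.

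**5. What would reporting error do?** This is an illustration on assumed inputs, since the article gives none. Let the true session count have standard deviation s between patients, and let reporting add independent random error with standard deviation e. With 80 per arm, the standard error of the between-arm difference in mean sessions is √(s² + e²) × √(2/80). Relative to error-free counts it grows by the factor √(1 + e²/s²).

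| Assumed s | Assumed e | Standard error | Factor |
|---|---|---|---|
| 3 | 0 | 0.474 | 1.000 |
| 3 | 1 | 0.500 | 1.054 |
| 3 | 3 | 0.671 | 1.414 |
| 5 | 0 | 0.791 | 1.000 |
| 5 | 1 | 0.806 | 1.020 |
| 5 | 3 | 0.922 | 1.166 |

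Over these assumptions the loss of precision runs from 2% to 41%. Random error of the same kind in both arms does not bias the difference in means. Bias needs misreporting or missingness that is related to the number of sessions and unequal between arms, and the article holds nothing from which to estimate that.

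**The case against.** **The article may not exclude the forms.** It speaks of a combination of questionnaires without naming a respondent, the table of instruments is not shown, and a condensed article may leave the source of each cost item to the full protocol. This stands in part: the sponsor may already intend to use the forms. But the article does name a source, and it is not the forms, so the point is more than absent detail.

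**Therapists are kept out of outcome measurement.** Medical consumption is a listed secondary outcome, so therapist records seem to conflict with Blinding. This stands as something to reconcile. An attendance count records what was delivered and leaves little room for judgement. The forms are also described as recording the process, and their content is not shown, but a form per session is enough for a count.

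**Stronger readings that the article does not support.**

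- A reader might infer that missing session counts will be imputed. The sentence "For missing data, imputation techniques will be used" stands in the paragraph on clinical effectiveness. The cost paragraph has no missing-data rule, and neither costs nor sessions are named.
- A reader might call study physiotherapy the main cost. The statement that "physiotherapy accounted for 84% of the total direct medical neck pain costs in 1996" is a background figure limited to direct medical costs. The trial also counts sick leave and disability, whose share is not given.
- A reader might say that treatment volume differs between arms by design. Both arms have the same cap and session length. The planned contrast is in content and approach.
- A reader might turn the 10% dropout and 20% loss to follow-up in Analyses into 16 and 32 of 160 patients without a count. Those percentages are triggers for a per-protocol analysis, not expected rates. A patient lost at 26 or 52 weeks may already have reported treatment at 4 or 9 weeks or at Ts.
- A reader might put a figure on the bias. If responders attended 14 sessions and non-responders 6, and non-responders were treated like responders, the mean would be overstated by 0.10 × 8 = 0.8 session at 10% non-response and by 0.20 × 8 = 1.6 at 20%. Every input is assumed, so the result only restates the assumptions.

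**Conclusion.** The point holds as a matter of data source. The article takes the volume of study treatment from questionnaires, while a contemporaneous record of each session exists in both arms and is not linked to costing. Session counts are therefore exposed to recall error and missing questionnaires that could largely be avoided.

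The conclusion rests on two readings: that the cost questionnaires are completed by patients, and that one form is completed for each session attended. The first is the natural reading but is not stated outright.

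The size of the error cannot be computed from the article. The 2% to 41% range for lost precision depends wholly on assumed standard deviations, and no bias is demonstrated. The consequence is confined to the cost side of the first aim. The primary outcome, the clinical comparison and the sample size are not affected. This is a cheap improvement, not a flaw that threatens the trial.

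**What to change.** In Outcome measurement:

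- State that the number of study sessions delivered is counted from the per-session forms, for every randomised patient in both arms.
- Keep the mailed questionnaires for what the forms cannot show: additional therapy, sick leave and disability.
- Use the patient-reported session count only as a cross-check, or where forms are missing.
- Add that the count is a treatment-delivery record and not an outcome assessment, so that it is consistent with Blinding.

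If the forms are already meant to serve this purpose, one sentence saying so is enough.

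The cost is a change of wording and data entry from forms that are completed anyway. The downside is reliance on unblinded therapists for a simple attendance count, which the patient's own report can check.

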### Analyses

Descriptive statistics will be used to examine comparability of baseline data between PT and GAP, and to check if randomisation was successful. Before this analysis, decisions about differences considered to be clinically relevant are made and, if necessary, adjustment will be made for these differences in multivariate analysis. Further, all outcome data will be screened for normality and, if necessary, logarithmic transformations or non-parametric methods of analysis will be applied.

The first aim is to evaluate the clinical and cost effectiveness of GAP compared to PT. Clinical effectiveness will be examined with a Student's t-test (continuous), a Chi-square test (dichotomised) or a Wilcoxon test (not normally distributed) according to the intention-to-treat principle. This means that patients will be analysed in the treatment group to which they are randomly allocated. For missing data, imputation techniques will be used. When the dropout rate is 10% or more, or loss to follow-up is 20% or more, per-protocol analysis will be performed. The results on primary outcome will be dichotomised into improved versus not improved. Improved implies completely recovered and much improved, whereas not recovered implies slightly improved, not changed, slightly worsened, much worsened, and worse than ever [31].

Cost effectiveness will be calculated from a societal perspective. Costs (direct as well as indirect) will be related to the treatment effects, based on the primary outcome measure, by calculating cost-effectiveness ratios.

The second aim is to identify subgroups of patients that benefit most from one of the two treatments. The following subgroups will be investigated: duration and severity of the complaint, depression, and fear of movement.

The third aim is to identify important variables for recovery. For this purpose multivariate analysis will be performed to investigate the influence of prognostic variables and patient characteristics on the outcome. Separate analyses will be conducted to investigate prognostic factors for short-term (3 months) and long-term (12 months) recovery.

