### Randomisation

An independent examiner using a computer-generated randomisation schema performs randomisation. To prevent unequal distribution, patients are pre-stratified based on three important prognostic factors: gender, age and the severity of the complaint, which are recorded at baseline [27]. Further, unequal group sizes are prevented by using a 6-block randomisation that equalizes allocation to the two treatment groups per stratum after every sixth patient [28]. After randomisation, patients choose a physiotherapist within the allocated treatment group. Then, to ensure that the treatment starts as soon as possible, the research assistant makes the first appointment for treatment.

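### Randomisation is stratified by gender, age and severity, but the treatment comparison leaves these factors out, and the conditional adjustment rule will very probably not bring them in

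*Protocol article*

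**What the plan says.** Under Randomisation, "patients are pre-stratified based on three important prognostic factors: gender, age and the severity of the complaint, which are recorded at baseline". Allocation within strata is restricted by "using a 6-block randomisation that equalizes allocation to the two treatment groups per stratum after every sixth patient".

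Under Analyses, clinical effectiveness is to be examined with a "Student's t-test (continuous), a Chi-square test (dichotomised) or a Wilcoxon test (not normally distributed) according to the intention-to-treat principle". For the primary outcome, GPE, this means the chi-square test, because "The results on primary outcome will be dichotomised into improved versus not improved". None of the named tests includes a stratification factor.

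The one route to adjustment of the treatment comparison comes earlier in the same section. Baseline data are compared between arms. "Before this analysis, decisions about differences considered to be clinically relevant are made", and then "if necessary, adjustment will be made for these differences in multivariate analysis". The multivariate analysis under the third aim concerns predictors of recovery, not the treatment effect.

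**The concern.** Stratifying on a prognostic factor removes its contribution from the real variability of the difference between arms. A test that ignores the factor still charges for that contribution, so its standard error is too large. It rejects a true null less often than the nominal 5%, and it misses real effects more often than it needs to.

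The conditional rule does not repair this. It is triggered by imbalance, and stratified blocks prevent imbalance in exactly these three factors. It can therefore admit a variable that happens to differ at baseline while leaving out the ones the authors call prognostic. The final model for the primary comparison is not known until the baseline data are in.

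At stake are some points of power on GPE, some precision on the continuous outcomes, and a primary model that could be fixed in advance but is not.

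**Working it through.** **The plan's own figure.** Sample size gives 160 patients (80 per arm) for a 20-point difference in GPE with 80% power. Alpha, sidedness and control rate are not stated. Assume two-sided 5% and use n per arm = [1.96·√(2p̄q̄) + 0.842·√(p1q1 + p2q2)]² / 0.2².
- 20% vs 40%: (1.270 + 0.532)² / 0.04 ≈ 81.2, so 82 per arm and 164 in total. This is close to 160.
- 40% vs 60%: (1.386 + 0.583)² / 0.04 ≈ 96.9, so 97 per arm and 194 in total. With 160 patients the power is 72%.

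The 160 therefore cannot be reproduced uniquely. The calculations below use 40% vs 60% as an illustration.

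**Will the rule pick up the stratification factors?** From the article: blocks of 6, 1:1, 160 patients. Assumed: each factor has two levels with half the patients in each (2 × 2 × 2 = 8 strata), and a difference counts as relevant above 10 percentage points.
- Only the last, incomplete block of a stratum can be unbalanced. With k patients in it, the variance of the difference in arm counts is k(6−k)/5. Averaged over k = 0 to 5 this is (0 + 5 + 8 + 9 + 8 + 5)/30 = 1.167.
- The difference between arms in a factor's proportion is about (D1 − D0)/160, where D1 and D0 are the count differences in its two levels. Over 8 strata its SD is √(8 × 1.167)/160 = 3.06/160 = 1.9 points. Ten points is 5.2 SDs away.
- With 18 strata (2 × 3 × 3, also assumed) the SD for gender is √(18 × 1.167)/160 = 2.9 points, and 10 points is 3.5 SDs away.
- For a binary variable with 50% prevalence that is not stratified on, the SD is √(0.25 × 2/80) = 7.9 points. Ten points is 1.26 SDs, exceeded in about 21% of trials.

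In a simulation with 8 strata (6,000 trials per setting), no stratification factor differed by more than 10 points in any trial. The conditional rule gave the same results as the unadjusted test throughout.

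**Type I error by formula.** The chi-square test uses the total variance p(1−p) = 0.4 × 0.6 = 0.24. Under stratification only the within-stratum part, the mean of p_s(1−p_s), is left. The true error is about 2·Φ(−1.96·√(0.24/within)). The odds ratios (ORs) of the three factors are assumptions.
- ORs 1/1/1: within 0.240, error 5.0%.
- ORs 1.3/1.5/2: within 0.230, error 4.5%.
- ORs 1.5/2/3: within 0.217, error 3.9%.
- ORs 2/3/4: within 0.200, error 3.2%.

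**Simulation, 40% vs 60%, two-sided 5%.** The adjusted analysis is logistic regression on arm and the three factors.

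| Assumed ORs | Type I, chi-square | Type I, adjusted | Power, chi-square | Power, adjusted | Gain (points) |
|---|---|---|---|---|---|
| 1/1/1 | 5.0% | 5.2% | 72.5% | 73.0% | 0.5 |
| 1.3/1.5/2 | 5.1% | 5.8% | 70.6% | 72.6% | 2.0 |
| 1.5/2/3 | 4.0% | 5.1% | 73.9% | 77.6% | 3.7 |
| 2/3/4 | 3.3% | 5.3% | 71.9% | 78.6% | 6.7 |

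The simulation error (SE) of a type I rate near 5% is √(0.05 × 0.95/6000) = 0.28 points. The chi-square column agrees with the formula to within about two SEs. A Cochran-Mantel-Haenszel (CMH) test by stratum gave nearly the adjusted power (72.8%, 72.2%, 77.2%, 78.3%).

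A separate simulation (4,000 trials) used log-odds of 1.0 for severity and 0.5 each for age and gender, that is ORs of about 2.7, 1.6 and 1.6. Its adjusted analysis was a linear probability model with robust variance and stratum covariates. Type I error was 4.0% unadjusted vs 5.2% adjusted, and power 72.6% vs 76.7%. With log-odds 1.5/0.75/0.75 (ORs about 4.5, 2.1 and 2.1) the figures were 3.1% vs 5.1% and 67.0% vs 73.2%, a gain of 6.2 points.

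**Continuous outcomes measured at baseline.** Let ρ be the baseline to follow-up correlation (assumed). Relative to a t-test on final scores, the ANCOVA variance is 1 − ρ². Relative to a t-test on change scores it is (1 − ρ²)/[2(1 − ρ)] = (1 + ρ)/2.
- ρ = 0.3: 0.91 against final scores, 0.65 against change. Against final scores this is worth 160/0.91 ≈ 176 patients.
- ρ = 0.5: 0.75 and 0.75, worth 160/0.75 ≈ 213.
- ρ = 0.7: 0.51 and 0.85, worth 160/0.51 ≈ 314.

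**The case against.** The strongest defence is that the unadjusted comparison is valid. Stratification with an unadjusted test does not inflate false positives, and if the factors are only weakly prognostic almost nothing is lost. That stands. The article calls the factors important but gives no strength, so the size of the loss is conditional on assumed odds ratios.

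A reader might also infer several stronger points that the document does not support.
- *That adjustment is chosen freely after seeing the data.* It is not. Relevance is decided before the baseline comparison, and the rule looks at baseline variables, not outcomes. What remains is that the article gives no thresholds and the covariate set still depends on observed imbalance.
- *That the rule selects covariates regardless of prognostic value.* The article does not say which variables qualify, or whether prognostic value counts when a difference is called clinically relevant.
- *That the trial is already short of power.* Alpha and control rate are not stated. At 20% vs 40%, 160 patients give about 79% power; the 72% applies at 40% vs 60%.
- *That continuous outcomes are analysed without their baseline value.* The article names a t-test but does not say whether final or change scores are tested, and a change score uses the baseline.

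The number of strata is also assumed, since no cut-points are given for age or severity. More strata leave more incomplete blocks, so selection of a stratification factor is improbable rather than impossible.

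This is not a matter simply left to an analysis plan. The article itself names the tests and states the adjustment rule.

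**Conclusion.** The point holds as a loss of efficiency and a model not fixed in advance, not as a threat to validity. The design stratifies on three factors, the named treatment comparison omits them, and the conditional rule will very probably never admit them. Under assumed odds ratios from 1 to about 4.5, the chi-square type I error goes from about 5% to a little above 3%, and the power given up goes from about 0 to 6-7 points. Adjustment costs nothing material when the factors turn out not to predict outcome (72.5% vs 73.0%). For continuous outcomes the ANCOVA gain over a t-test on final scores is a variance reduction of 9% to 49% for correlations of 0.3 to 0.7. ANCOVA is at least as efficient as a t-test on change scores.

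The prognostic strengths, the eight strata, the 40% control rate, the two-sided 5% level, the 10-point threshold and the correlations are all assumptions. The change should be made. Confidence is high on what the text says and on the direction, and moderate on the size.

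**What to change.** Under Analyses, pre-specify gender, age and severity, in the form used for stratification, as fixed covariates in the treatment comparison.
- **Dichotomised GPE:** logistic regression on arm and the three factors, reported as a standardised risk difference so that the result stays on the 20-point scale of the sample size. A CMH test stratified by the randomisation strata is an acceptable alternative.
- **Continuous outcomes measured at baseline:** a linear model (ANCOVA) with the same factors plus the baseline value of the outcome.
- **Sensitivity analyses only:** the unadjusted t, chi-square and Wilcoxon tests, and any adjustment triggered by baseline imbalance. If the latter is kept, state its thresholds and candidate variables.
- **Baseline tables:** descriptive, with no role in choosing the primary model.

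The cost is analysis wording. The stratification factors are already recorded at baseline, and no extra patients are needed.
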